### Follow-up assessment after six months (T2)

Six months after the end of the sessions funded by the PB, therapists will provide information on the continuation vs. interruption of their psychological interventions and eventually report on their patients’ diagnosis (APA, 2022) and overall mental well-being (GAF).

Adult patients will report on productivity, psychological distress (CORE-10), emotion regulation (ERQ), anxiety (GAD-7) and depression symptoms (PHQ-9), epistemic trust (ETMCQ), and quality of life (EQ-5D). Adolescent patients will report on productivity, psychological distress (YP-CORE), behavioral problems (YSR), emotion regulation (ERQ), epistemic trust (ETMCQ), and quality of life (EQ-5D-Y).

## Data analyses

​​Statistical analyses will be conducted using R Core Team ver. 4.3.1 [57].

We will compute descriptive statistics for all study objectives, utilizing the *psych* package [58], to examine the participants’ general characteristics.

We will compute descriptive statistics to explore access to the PB by analyzing the demographic characteristics of adhering therapists and patients (Objective 1). This will allow us to examine the characteristics of participants in terms of age, gender, socioeconomic status, and geographical location, among other pertinent variables (i.e., therapists’ expertise and theoretical framework; patients’ diagnostic information and severity of psychological distress).

To assess the impact of interventions on the psychological well-being of users (Objective 2), we will employ mixed models with random coefficients across participants using the R package *lme4* [59].

We conducted a power analysis using a simulation-based approach to estimate the minimum sample size required to detect a small effect size. The simulations were conducted using the R package *simr* [60]. The data simulation model was configured with random intercepts for participants. We assumed that all random variances were equal to 1, and the effect size of the outcome (slope) was computed to correspond to a Cohen’s d of 0.20 [61]. The correct slope coefficient value was calculated using the formulas described in Judd, Westfall, and Kenny [62]. Setting the simulations model with coefficients for the target effect random across participants ensures a pessimistic, and therefore more conservative, estimation of the minimum number of participants required [63]. According to the design, we varied the number of participants until the simulations showed the required power (1 − β = 0.80). The results of the power analysis indicated that a sample of N = 220 participants would provide a power of 0.80, and a sample of N = 290 would yield a power of 0.90. Accounting for a 50% dropout rate, we will to collect a minimum of 435 participants.

To assess the economic impact of the PB (Objective 3), we will conduct a cost-effectiveness analysis (CEA) [64]. The calculation will include both direct and indirect costs between the baseline (T0) and post-intervention (T1) assessments. Direct healthcare costs will encompass the costs of the psychological intervention and any related healthcare costs. These costs will be compared to data on standard care from the Italian Ministry of Health to calculate the incremental costs of the intervention. Indirect costs, or productivity losses, will be estimated by multiplying the number of days of work/university/school lost due to psychological problems (as reported by participants) by an average daily wage (for work) or an estimated cost of a lost day of education (for university/school). The effectiveness of the intervention will be measured using the EQ-5D, which will be used to estimate Quality Adjusted Life Years (QALYs). The incremental cost-effectiveness ratio (ICER) will be calculated as the cost difference between the PB intervention and standard care from T0 to T1, divided by the difference in QALYs over the same period. The resulting ICER will represent the additional cost per QALY gained by the PB intervention compared to standard care. A sensitivity analysis will be conducted to test the robustness of our findings to changes in key assumptions or parameters, including the unit costs used to calculate direct costs and the valuation of lost productivity. This analysis will be conducted in accordance with standard guidelines for conducting and reporting CEAs, such as the Consolidated Health Economic Evaluation Reporting Standards (CHEERS) statement [65]. The power analysis from the *pwr* package in R [66] indicated that for a paired t-test with a small effect size (Cohen’s d = 0.20), a power of 0.80, and a significance level α = 0.05, you would need a sample size of approximately n = 199 pairs of observations.

To assess the hypotheses on emotion regulation and epistemic trust (Objective 4), we use mixed models with random coefficients across participants. We conducted a power analysis using a simulation-based approach to estimate the minimum sample size required to detect a small effect size using the R package ‘simr’ [60]. We included the interaction of time with the transdiagnostic factor (i.e., emotion regulation) and their main effects. The results of the power analysis indicated that a sample of N = 200 participants would provide a power of 0.80, and a sample of N = 280 would yield a power of 0.90. Accounting for a 50% dropout rate, we will to collect a minimum of 420 participants.

The number of sessions conducted will be included as a covariate in all our multilevel models to control for potential confounding effects. This allows us to account for variability in therapy length, as the number of sessions may range from 4 to 10 per the parameters of the PB, but may extend beyond that if patients continue the intervention. Moreover, to account for differences between individuals that where already in treatment and not, we will include group variability in our models.

We will conduct post-hoc tests and sensitivity analyses to explore all findings further.

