**Methods:**

The study involves licensed psychotherapists and their patients, both adults and adolescents, benefiting from the Psychological Bonus. Data collection is underway and set to conclude in December 2023. Psychotherapists will provide diagnostic information and assess patient functioning. In addition, patients will be evaluated on mental health aspects such as clinical symptoms, emotion regulation, epistemic trust, and quality of life. We will employ linear mixed-effects models to analyze the outcomes, accounting for both fixed and random effects to capture the hierarchical structure of the data.

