### Sampling plan

Data collection will include two samples. The first sample will consist of therapists registered with the National Board of Italian Psychologists, adhering to the Italian Psychologist Bonus initiative. The second sample will consist of participating therapists’ patients encompassing adults over 18 years old and adolescents aged between 14 and 18 using the Psychologist Bonus.

Therapists are recruited via online newsletters and web news promoted by the National Board of Italian Psychologists. Patients are recruited via their therapists’ participating in the study.

Before participating in the study, all participants will provide informed consent. For under-age participants, informed consent will be obtained from adolescents and their parents/legal guardians. Participation is entirely voluntary. As an incentive for enrollment, therapists can participate in a training course on psychological assessment for free and obtain forty out of the fifty yearly professional mandatory training credits [31].

Each therapist is assigned a unique six-letter reference code (i.e., ABCDEF). To ensure patients’ matching, the therapist will assign their unique code and a number for every patient enrolled (i.e., ABCDEF-1 for patient number 1, ABCDEF-2 for patient number 2, etc.). All self-report questionnaires are completed via a secure web link to ensure anonymity on the Qualtrics platform.

Our target sample size, is a minimum of 450 therapists and 450 patients (adults and adolescents) to achieve sufficient power for the study.

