Third, in line with recent advancements in psychotherapy research, we aim to adopt a patient-specific, or “tailored,“ approach, exploring “what works for whom,“ as described by Peter Fonagy: indeed, the PsyCARE will provide findings to identify the therapeutic elements associated with patients’ improvement and determine which patients may benefit the most from the bonus sessions and specific psychotherapeutic techniques adopted [67, 68]. For example, we will consider between-subjects variability on the longitudinal trajectories of psychological symptoms accounting for different diagnostic presentations and controlling for the therapists’ different theoretical frameworks. Moreover, the study will allow the evaluation of the effectiveness of a psychological intervention through the observation of transdiagnostic factors (i.e., emotion regulation, epistemic trust) to open a window of understanding of the mechanisms of change that can be influenced by psychological interventions and can, in turn, contribute to the reduction of symptomatic manifestations.

Fourth, the PsyCARE study aligns with the need to make scientific results replicable. Indeed, one of the major limitations of research in psychology is the inability to replicate the results of studies on different samples. Although the study guarantees a sufficient number for the reliability of its results, it will be necessary to replicate its findings in other contexts and populations. Thus, all data and materials will be available on the Open Science Framework [69].

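### The stated models and the Objective 2 power simulation leave out clustering of patients within therapists; the cost depends on how many patients each therapist contributes

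*Protocol article*

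**What the plan says.** All references are to the protocol article.

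- **Models (Data analyses).** For Objective 2: "we will employ mixed models with random coefficients across participants". For Objective 4: "we use mixed models with random coefficients across participants". Neither statement names a therapist term. The adjustments listed there are number of sessions and whether the patient was already in treatment.
- **Power simulation for Objective 2 (Data analyses).** "The data simulation model was configured with random intercepts for participants". A later sentence in the same paragraph describes the target effect, too, as random across participants. No therapist level appears. The result is 220 participants for power 0.80 and 290 for 0.90. For Objective 4 the article gives the fixed terms of the simulation but not its random structure.
- **Recruitment (Sampling plan).** Patients enter the study through their participating therapists. The therapist labels each one with "their unique code and a number for every patient enrolled", as in ABCDEF-1 and ABCDEF-2. No maximum per therapist is set. The target is at least 450 therapists and at least 450 patients.
- **Therapist factors (Discussion).** Symptom trajectories are to be studied while "controlling for the therapists’ different theoretical frameworks".
- **Hierarchy (Abstract, Methods).** The models are described as "accounting for both fixed and random effects to capture the hierarchical structure of the data".

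**The concern.** The design has three levels: assessments at T0, T1 and T2 within patients, and patients within therapists. The stated random effects cover the first nesting and not the second. If some therapists' patients improve more than others', changes within a therapist are correlated, and a model that treats patients as independent credits the data with more information than they hold. Confidence intervals for the time effect become too narrow, and so do those for any factor that varies between therapists, such as theoretical framework. Entering that framework as a covariate does not cure this, because therapists who share a framework still differ.

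The power statement inherits the same gap. It is described as conservative because the target effect varies across participants, but variation across therapists is not part of it.

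**Working it through.** **Inputs from the article.** N = 220 for power 0.80 and N = 290 for 0.90 (Objective 2, d = 0.20); target of at least 450 patients and 450 therapists; 50% dropout. A significance level of 0.05 is stated only for the Objective 3 paired t-test; I assume it here too, two-sided.

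**Assumed inputs.** The article gives neither the intra-therapist correlation of change (ρ) nor the distribution of patients per therapist. All values below for ρ and for m, the completers per contributing therapist, are illustrations.

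**The plan's own figure.** I could not reproduce 220/290. Closed-form versions of the simulation give 196/263 or 262/350, depending on how d is scaled. Across all time codings and variance choices tried, the N for 0.80 runs from 49 to 523. The article does not give enough detail to choose between them, so this does not show 220/290 to be wrong. The two figures agree with each other: 220 × (3.2415/2.8016)² = 295, close to 290. I therefore take 220 = 0.80 as given and scale from it.

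**Completers.** 450 × (1 − 0.50) = 225, all taken in one model.

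**Formulas.**
- Design effect: DE = 1 + (m − 1)ρ
- Effective number: n_eff = 225/DE
- Power: Φ(2.8016 × √(n_eff/220) − 1.96)

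| m | ρ | DE | SE understated by factor | n_eff | Power |
|---|---|---|---|---|---|
| 1 | any | 1.00 | 1.000 | 225 | 0.81 |
| 2 | 0.03 | 1.03 | 1.015 | 218 | 0.797 |
| 2 | 0.05 | 1.05 | 1.025 | 214 | 0.790 |
| 3 | 0.05 | 1.10 | 1.049 | 205 | 0.771 |

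**Slack.** Power falls below 0.80 once DE exceeds 225/220 = 1.023. The margin is thin, but so is the shortfall over most of this range.

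**Does a ratio of 450:450 make m equal to 1?** Only if every therapist enrols exactly one patient. The relevant size is the patient-weighted one, E[m²]/E[m]. If enrolment counts were Poisson with mean 1 (an assumption), it would be (1 + 1)/1 = 2 at enrolment. After independent 50% dropout the mean is 0.5 and the size is (0.5 + 0.25)/0.5 = 1.5. With ρ = 0.05, DE = 1 + 0.5 × 0.05 = 1.025, n_eff = 220 and power is 0.799. Modest unevenness around the planned ratio is therefore close to harmless.

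**Type I error.** A simulation of 4,000 runs at N = 220, with ρ of 0.05 to 0.10, tested mean change while ignoring therapists. The nominal 5% test rejected at 0.049–0.054 with one patient per therapist, 0.051–0.056 with two and 0.073–0.096 with five. The Monte Carlo standard error is √(0.05 × 0.95/4000) = 0.003.

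**The case against.** The strongest reply is the planned ratio. With 450 therapists for 450 patients the mean is one patient each, the design effect is 1.00, and 220/290 stands. This is right as far as it goes, and it is why the point is conditional. It does not remove the point, because both targets are minimums, no cap is set, and some enrolled therapists may contribute no patient while others contribute several.

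A second reply is that a condensed article need not give the full model formula, and that naming participants does not exclude another level. That has some force for the models. It has less for the power simulation, which is reported as completed with random effects for participants. There, participants must mean patients, since the resulting 435 is set against the patient target.

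A reader might go further in four ways that the article does not support:

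- **That standard errors and power are too optimistic outright.** This depends on cluster sizes and a correlation that the article does not give.
- **That the patient codes show several patients per therapist are expected.** The codes serve matching. They permit several patients but forecast nothing.
- **That the abstract's statement on hierarchy is contradicted.** Repeated assessments within patients are a hierarchy, and random coefficients across participants model it. The sentence is vague, not false.
- **That power falls to about 0.69.** This follows from m = 5 and ρ = 0.08 (DE 1.32, n_eff 170). But five completers per therapist means only 225/5 = 45 contributing therapists, against a target of at least 450. If five is the number recruited, independent 50% dropout leaves each completer with 4 × 0.5 = 2 others. Then DE = 1 + 2 × 0.08 = 1.16, n_eff = 194 and power is about 0.75.

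Nor does the article say how therapist-level covariates enter the model; it says only that framework is controlled for.

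**Conclusion.** The omission is plain in the text: no therapist level appears in the stated Objective 2 and 4 models or in the Objective 2 power simulation, although the design creates one and the code identifies it. Its consequence is conditional. With one patient per therapist it is nil. With two or three completers per therapist and ρ of 0.03 to 0.05, standard errors are understated by about 1.5% to 5%, and power is about 0.80 to 0.77 instead of 0.81. Larger losses need recruitment concentrated in far fewer therapists than planned. These figures rest on assumed correlations and cluster sizes, on 220 = 0.80 taken as stated, and on 225 completers. This is a cheap improvement worth making, not a flaw that undermines the study.

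**What to change.** 1. **Account for therapist in all Objective 2 and 4 models**, using the six-letter code already collected. Use either therapist-clustered robust standard errors or a therapist random intercept, and add a therapist random effect on time where it is estimable. An intercept alone absorbs differences in level between therapists but hardly changes the standard error of within-patient change. If the random effect on time cannot be estimated, the clustered standard errors are therefore what protects the time effect.
2. **Fix the fallback in advance.** State what happens with a singular or non-convergent fit, for example a return to the participant-level model with therapist-clustered standard errors. Do not leave it to inspection of the estimated variance.
3. **Restate the power.** Give the expected number of patients per therapist and a range for the intra-therapist correlation of change, with power conditional on both; or show from the enrolment counts that the design effect is negligible.
4. **Make the abstract's wording specific** by naming the levels that the models cover.

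The cost is an extra term or a different variance estimator, slightly wider confidence intervals, and possible singular fits if most therapists contribute one patient. No new data are needed.

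### The minima of 435 and 420 allow for a one-third loss, not the stated 50% dropout; at 50% the 450-patient target supports the required 0.80 power but not 0.90

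*Protocol article*

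**What the plan says.** Three places in the protocol article bear on this.

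- **Data analyses, Objective 2.** The simulation criterion is stated: "we varied the number of participants until the simulations showed the required power (1 − β = 0.80". The result is that "a sample of N = 220 participants would provide a power of 0.80, and a sample of N = 290 would yield a power of 0.90". The next sentence reads: "Accounting for a 50% dropout rate, we will to collect a minimum of 435 participants".
- **Data analyses, Objective 4.** A second simulation found that "a sample of N = 200 participants would provide a power of 0.80, and a sample of N = 280 would yield a power of 0.90". The next sentence reads: "Accounting for a 50% dropout rate, we will to collect a minimum of 420 participants".
- **Sampling plan.** The overall recruitment target is given without a power figure: "Our target sample size, is a minimum of 450 therapists and 450 patients (adults and adolescents) to achieve sufficient power for the study".

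For Objective 3, the Data analyses section also reports 199 pairs for a paired t-test at power 0.80 and α = 0.05. No dropout allowance is attached to that number.

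**The concern.** To have n participants left after losing a fraction d, one must enrol n / (1 − d). With d = 0.50 that doubles the number. Neither stated minimum is double any of the reported sample sizes; each is one and a half times the larger one. The plan therefore appears to have added 50% to the sample instead of allowing for the loss of 50% of it.

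What is at stake is how the sample-size justification will be read. Someone who sees 290 followed by 435, or 280 followed by 420, will take it that the larger number is still there after half the patients have gone. It is not. The same slip occurs in both objectives, and these are the only figures in the article that link the dropout assumption to recruitment.

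**Working it through.** **Inputs, all from Data analyses and Sampling plan.** Objective 2: 220 (power 0.80), 290 (0.90), minimum 435. Objective 4: 200 (0.80), 280 (0.90), minimum 420. Objective 3: 199 pairs (0.80). Stated dropout d = 0.50 for Objectives 2 and 4. Patient target 450.

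**Step 1: reproduce the stated minima.**

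| Rule | Objective 2 | Objective 4 | Matches 435 and 420? |
|---|---|---|---|
| 0.90-power n × 1.5 | 290 × 1.5 = 435 | 280 × 1.5 = 420 | Both, exactly |
| 0.90-power n / 0.5 | 290 / 0.5 = 580 | 280 / 0.5 = 560 | Neither |
| 0.80-power n / 0.5 | 220 / 0.5 = 440 | 200 / 0.5 = 400 | Neither exactly (435 is close to 440; 420 is not close to 400) |
| 0.80-power n × 1.5 | 220 × 1.5 = 330 | 200 × 1.5 = 300 | Neither |

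Only the first rule gives both figures. No single power level combined with 50% dropout gives both.

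**Step 2: the dropout rate that the minima actually cover.** 1 − 290/435 = 1 − 280/420 = 0.333, so one third.

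**Step 3: who remains at 50% dropout.**

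- 435 × 0.5 = 217.5, against 220 for 0.80 and 290 for 0.90.
- 420 × 0.5 = 210, against 200 for 0.80 and 280 for 0.90.
- 450 × 0.5 = 225, against 220 (Objective 2), 200 (Objective 4) and 199 (Objective 3) for 0.80. All three are met.

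**Step 4: approximate power at those numbers.** Let the non-centrality grow with √n and calibrate it on the plan's own points. Two-sided α = 0.05 is assumed, because the article gives α only for the Objective 3 t-test. Then power = Φ(c × √(n/n₀) − 1.960), with c = 1.960 + 0.842 = 2.802 when n₀ is the 0.80-power number, and c = 1.960 + 1.282 = 3.242 when n₀ is the 0.90-power number.

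| Remaining n | Calibrated on the 0.80 point | Calibrated on the 0.90 point |
|---|---|---|
| Objective 2, 217.5 (from 435) | 0.796 | 0.802 |
| Objective 2, 225 (from 450) | 0.809 | 0.815 |
| Objective 4, 210 (from 420) | 0.819 | 0.802 |
| Objective 4, 225 (from 450) | 0.844 | 0.828 |

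The scaling is only a guide. It predicts a ratio of 1.34 between the 0.90 and 0.80 sample sizes, while the plan's own ratios are 290/220 = 1.32 and 280/200 = 1.40. The plan's simulations were not rerun.

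**Step 5: dropout at which 450 still gives 0.90.** Objective 2: 1 − 290/450 = 0.356. Objective 4: 1 − 280/450 = 0.378.

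**The case against.** The strongest reply is that nothing the plan promises is lost. The article names 0.80 as the required power and reports the 0.90 sample sizes as a further result. The operative recruitment number is 450, not 435 or 420, and half of 450 still exceeds the 220, 200 and 199 needed for 0.80. This stands, and it limits the point.

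A reader might infer from the exact multiples that the study was sized for 0.90, and hence that its type II error is about 19% where 10% was promised. The documents do not support that. No sentence sets 0.90 as the target, so the link to 290 and 280 is an inference from arithmetic, and at a required power of 0.80 the plan already accepts a 20% type II error. A reader might likewise infer that 450 is too few, or that it must rise to 580 and 560. That does not follow either: the Sampling plan attaches no power figure to 450, and the required 0.80 is met there.

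Two further replies have some force. First, the shortfall of 435 for Objective 2 is two or three participants, and whether the approximate power falls just below or just above 0.80 depends on which of the plan's points is used for calibration. Second, the analyses for Objectives 2 and 4 are mixed models over three time points, so a patient lost after the second assessment still contributes. Counting completers only is therefore somewhat conservative.

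None of this rescues the stated minima. Under the 0.80 reading, 50% dropout requires 440 and 400; under the 0.90 reading, 580 and 560. The article prints 435 and 420. Nor is this a detail left to a fuller document, because the figures and the dropout rate are both stated outright.

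**Conclusion.** Wrong as written, of moderate severity. The dropout inflation is miscalculated in both places: the printed minima correspond to 33% attrition, not 50%. At the stated rate they leave 217 or 218 and 210 participants, so the 0.90-power sample sizes from which they appear to be derived are not retained.

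The patient target of 450 is not undermined. At 50% dropout it leaves 225, enough for the required 0.80 in Objectives 2, 3 and 4, with a margin of only five participants in Objective 2. It does not give 0.90; that would need dropout of no more than about 36% (Objective 2) or 38% (Objective 4).

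The counts follow from the plan's figures alone. The power values at 225, about 0.81 and 0.83–0.84, rest on more: the plan's simulated sample sizes taken as given, two-sided α = 0.05, square-root scaling, completers only, and all 450 patients, adults and adolescents together, entering the analysis in question.

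**What to change.** Keep the 450-patient target and correct the text in one of two ways.

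(a) If 50% dropout is the intended assumption, state that at this rate the design supports the required power of 0.80. Replace 435 by 440 for Objective 2 and 420 by 400 for Objective 4. State that 450 enrolled leaves 225, and that 0.90 is reached from 450 only if dropout is at most about 36% (Objective 2) or 38% (Objective 4). If power at 225 is to be quoted, rerun the simulations at that number; the approximate values above should not go into the plan as simulation output.

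(b) If one-third attrition was meant, change the dropout rate to about 33% in both places and keep 435 and 420.

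Either way enrolment, design and analysis are unchanged. The cost is a few sentences, plus a short simulation run if power at 225 is quoted. The downside is that the justification looks less favourable: lower stated power under (a), or a smaller dropout allowance under (b).

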## Introduction

### A global mental health emergency

A recent epidemiological study from 204 countries and territories highlighted approximately 53 million cases of major depressive disorder and 76 million cases of anxiety disorders directly linked to the pandemic. Notably, the younger population experienced the most significant increase, with women being twice as affected as men by these disorders [1].

In Italy, the Mental Health 2021 report published by the Italian Ministry of Health in 2022 stated that 778,737 individuals sought assistance from public specialist mental health services during 2021. Furthermore, nationwide data showed that 3.3% of emergency room admissions (n = 479,276) were related to psychiatric issues. Among individuals seeking assistance for mental health-related problems, 14.6% resulted in hospitalization, while 72.1% were managed at home. Thus, 7 out of 10 individuals seeking mental health services do not present with severe enough conditions to require hospitalization but require some form of psychological support, nonetheless. Moreover, 39.6% of all admissions are diagnosed with neurotic and somatoform syndromes [2]. Available data supports the evidence that the current public mental health system does not adequately address chronic cases, sub-clinical severity, or those that do not involve emergency management.

According to the 2022 Organisation for Economic Co-operation and Development (OECD) report titled “Health at a Glance: Europe,“ there was an increase in unmet needs for mental health care during and after the pandemic, with 23% of adults reporting such conditions in spring 2022, compared to 20% in spring 2021. While comprehensive data remains limited, national estimates indicate that the prevalence of depressive symptoms during the pandemic was approximately twice as high as pre-pandemic levels in numerous European countries [3]. Also, when looking at children and adolescents, recent estimates from the World Health Organization indicate that one in six individuals aged 10–19 have a mental disorder, with depression, anxiety, and behavioral disorders being the primary causes of distress [4]. Similar figures have been confirmed in Italian adolescents by a recent literature review by Deolmi & Pisani (2020) that emphasized the high prevalence of anxiety and depressive symptoms among young Italians attributed to the pandemic, social isolation, and parental stress [5].

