## Discussion

The PsyCARE study’s primary goal is to provide systematic data on the Italian Government’s “Psychological Bonus” effectiveness in promoting access to psychological treatments. The study breaks ground in several ways.

First, the PB represents a first-time national initiative due to its promotion by the Ministry of Health outside the public healthcare system. However, funding is limited as only 10.52% of applicants will be allowed to benefit from professional interventions for psychological problems. The situation of public services in Italy has shown their struggle in responding to the great demand for intervention for psychological problems that do not require urgent treatment. This insufficient response risks contributing to the chronicization or worsening over time of situations that, if intercepted earlier, might instead have a different prognosis. Thus, the PsyCARE study will help provide more information on the effectiveness of the psychological interventions funded by the PB, both in lowering patients’ psychological distress and providing a cost-effective measure. Thus, the study’s data may help justify future financial allocations and influence policymakers to strengthen public and private services.

Secondly, PsyCARE will gather real-world data on the effectiveness of psychological interventions in reducing symptoms, with a particular focus on anxiety and depression. Indeed, the study seeks to integrate cross-sectional perspectives and evaluate the effects of short-term psychological interventions. The study’s results will potentially significantly contribute to the ongoing debate in psychotherapy regarding the role and impact of specific versus nonspecific therapeutic factors.

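### The cost-effectiveness analysis takes incremental cost against unmatched Ministry standard-care data that may not represent what Bonus users would otherwise get, and that figure alone can set the sign of the result

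*Protocol article*

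**What the plan says.** All references are to the protocol article.

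- **Data analyses, Objective 3.** On cost: "These costs will be compared to data on standard care from the Italian Ministry of Health to calculate the incremental costs of the intervention". The ratio is "calculated as the cost difference between the PB intervention and standard care from T0 to T1, divided by the difference in QALYs over the same" interval, and its interpretation is fixed in advance: "The resulting ICER will represent the additional cost per QALY gained by the PB intervention compared to standard care".
- **Same paragraph, sensitivity analysis.** Key assumptions or parameters will be varied, "including the unit costs used to calculate direct costs and the valuation of lost productivity". The choice of comparator is not named.
- **Introduction, A global mental health emergency.** After citing Ministry figures on specialist services, emergency attendance and hospital admission, the authors conclude that "the current public mental health system does not adequately address chronic cases, sub-clinical severity, or those that do not involve emergency management".
- **Discussion.** Public services have shown "their struggle in responding to the great demand for intervention for psychological problems that do not require urgent treatment". The Bonus is called a national first because of its "promotion by the Ministry of Health outside the public healthcare system".
- **Introduction, section on the Psychological Bonus.** Of 395,604 requests, 41,657 were accepted. The grant is at most 600, 400 or 200 euros by income band. People already in psychotherapy may use it.

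**The concern.** A comparator in a cost-effectiveness analysis should stand for what the same people would have received without the policy. The protocol justifies the Bonus by saying that public care serves non-urgent and sub-clinical cases poorly, and then takes public standard care as the alternative whose cost is subtracted. It states no restriction of those data to patients like the Bonus users. For a Bonus user the alternative could as plausibly be no care, a wait, or therapy paid for privately. The last applies especially to those already in treatment. The outcome models allow for that group, but the cost-effectiveness paragraph does not mention it.

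If the Ministry data describe a different case mix, part of the incremental cost will reflect who was compared rather than what the Bonus did. Cost-effectiveness is one of the primary outcomes listed in the Aims, and the Discussion expects the results to inform later funding decisions.

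**Working it through.** **Plan's own figure.** The only computed number for Objective 3 is 199 pairs (paired t-test, d = 0.20, power 0.80, α = 0.05). It reproduces two-sided: power is 0.8017 at n = 199 and 0.7997 at n = 198. It has no bearing on the comparator. The article gives no cost or QALY for standard care, so there is no ratio to reproduce.

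**Inputs from the article**
- Total funding: 10 + 15 = 25 million euros.
- Accepted applications: 41,657 of 395,604.
- Period of use: 180 days.

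**Inputs assumed here**
- The standard-care cost per patient, C_SC, is varied from 0 to 1,000 euros.
- The utility gain is 0.05, reached linearly over 180 days, with a range of 0.03 to 0.10. It is held fixed while C_SC varies.
- Only the subsidy and C_SC are counted. Other healthcare costs and productivity are left out.

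**Step 1: Bonus cost per beneficiary.** 25,000,000 / 41,657 = 600.1 euros, which equals the top grant. I use C_PB = 600.

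**Step 2: share unfunded.** 1 − 41,657/395,604 = 89.5%. Not receiving funded sessions was the usual result of applying. The article does not say what those applicants did next.

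**Step 3: QALY gain.** 0.05/2 × 180/365 = 0.0123.

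**Step 4: incremental direct cost and ratio.** ΔC = C_PB − C_SC; ICER = ΔC / 0.0123 (unrounded denominator used).

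| Assumed C_SC (euros) | ΔC (euros) | ICER (euros per QALY) |
|---|---|---|
| 0 | +600 | about 48,700 |
| 400 | +200 | about 16,200 |
| 600 | 0 | 0 |
| 1,000 | −400 | about −32,400 (apparent cost saving) |

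The sign of ΔC changes where C_SC passes about 600 euros. For users in the lower-grant bands it changes at 400 or 200 euros.

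**Step 5: utility assumption.** With C_SC = 0, a gain of 0.03 gives about 81,100 euros per QALY and a gain of 0.10 gives about 24,300. With any positive QALY gain, the sign depends on C_SC alone.

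**Step 6: does the planned sensitivity analysis cover this?** Varying unit costs re-prices the care counted. It does not change whose care is counted. The list is open-ended, so a comparator scenario could be added, but none is committed to.

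**The case against.** Comparing a new policy with standard care is a normal choice, and an article may leave the exact data source to a fuller plan. Several stronger readings that a reader might infer do fail on the documents:

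- **That Bonus users receive no public care.** The article calls public care inadequate or insufficient for such cases. It does not say that they go without it.
- **That the comparator patients are sicker, so incremental cost is biased downwards.** The Objective 3 text names no dataset, service or severity level. The Ministry figures in the Introduction are background and carry no costs. They include 72.1% managed at home and 39.6% of admissions with neurotic or somatoform diagnoses. No severity limit is set for Bonus users either, so neither case mix is known.
- **That hospital admissions alone would reverse the sign.** Applying the 14.6% hospitalised to an assumed 2,000 to 5,000 euros per admission gives 292 to 730 euros per person, with break-even near 4,110 euros (600/0.146). But the 14.6% follows the emergency-room sentence and may describe only those attenders. The sum also gives Bonus users no such costs and ignores the T0–T1 window. It cannot serve as an estimate.
- **That no funded sessions must be the base case.** Refused applicants are not sampled and their later care is unknown, so that base case would rest on assumption.
- **That the sensitivity analysis could not expose the problem.** Its wording is open-ended.

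These objections remove any claim about direction or size. They do not remove the central point: the article fixes both the comparison and how the ratio will be read, restricts the comparator in no way, and gives reasons of its own to doubt that it fits these users.

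**Conclusion.** The point holds in limited form. The comparator is external, unmatched and in tension with the study's own rationale. Its costs may come from a different, possibly more severe, population. The choice could move the incremental direct cost from about +600 euros, if the alternative costs nothing, through zero at about 600 euros to negative values above that. The direction and size of any actual bias cannot be determined from the documents.

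The 600-euro threshold rests on spreading the full 25 million euros over the accepted applications and on counting the subsidy alone. The ratios per QALY also rest on the assumed utility gain. This is worth correcting before analysis, because it governs what the cost-effectiveness conclusion can claim.

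**What to change.** In the Objective 3 paragraph of Data analyses:

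1. State which Ministry data are used. Restrict them to outpatient care for comparable presentations, mainly anxiety and depression, and scale them to the T0–T1 interval where the data allow.
2. Add the choice of comparator to the named sensitivity analyses, with at least two scenarios: no funded sessions, and continued self-paid therapy for patients already in treatment.
3. Word the conclusion as cost-effectiveness against the comparator used, and claim robustness only if it holds across these scenarios.

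The cost is some rewording and a few extra calculations, with no new data from participants. The added scenarios will rest partly on assumed costs, the Ministry data may not allow the restriction in full, and the result may turn out less favourable to the Bonus.
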